## Abstract

**Background:**

Excessive body weight, low physical activity and excessive sedentary time in youth are major public health concerns. A new generation of video games, the ones that require physical activity to play the games –i.e. active games- may be a promising alternative to traditional non-active games to promote physical activity and reduce sedentary behaviors in youth. The aim of this manuscript is to describe the design of a study evaluating the effects of a family oriented active game intervention, incorporating several motivational elements, on anthropometrics and health behaviors in adolescents.

**Methods/Design:**

The study is a randomized controlled trial (RCT), with non-active gaming adolescents aged 12 – 16 years old randomly allocated to a ten month intervention (receiving active games, as well as an encouragement to play) or a waiting-list control group (receiving active games after the intervention period). Primary outcomes are adolescents’ measured BMI-SDS (SDS = adjusted for mean standard deviation score), waist circumference-SDS, hip circumference and sum of skinfolds. Secondary outcomes are adolescents’ self-reported time spent playing active and non-active games, other sedentary activities and consumption of sugar-sweetened beverages. In addition, a process evaluation is conducted, assessing the sustainability of the active games, enjoyment, perceived competence, perceived barriers for active game play, game context, injuries from active game play, activity replacement and intention to continue playing the active games.

**Discussion:**

This is the first adequately powered RCT including normal weight adolescents, evaluating a reasonably long period of provision of and exposure to active games. Next, strong elements are the incorporating motivational elements for active game play and a comprehensive process evaluation. This trial will provide evidence regarding the potential contribution of active games in prevention of excessive weight gain in adolescents.

**Trial registration:**

Dutch Trial register NTR3228.

## Background

Excessive body weight, low physical activity and excessive sedentary time in youth are major public health concerns [1-3], especially among children and adolescents from lower educated [4] and ethnic minority parents [5]. Obesity is associated with an increased risk for a range of chronic diseases and presents a major burden of disease and health care spending [6-8]. One of the life stages that may play a critical role in the development and persistence of obesity and related co-morbidities into adulthood is adolescence [9,10]. The adolescent period is characterized by low physical activity, high levels of sedentary behavior and changes in body composition (amount and location of body fat), making adolescents an important target group for preventive strategies [9].

Overweight and obesity generally result from a long-term imbalance between energy intake (determined by dietary intake) and energy expenditure (mainly determined by physical activity and sedentary behaviors) [11]. Regarding the latter, sedentary activities such as watching TV and playing video games, have been found to be associated with negative health outcomes such as overweight and obesity, partly independent of diet and moderate to vigorous physical activity [12-16]. It has been suggested that reductions in sedentary behavior may be as effective as or even more effective than increasing physical activity directly in decreasing BMI, and percentage overweight [17]. A major and increasing contributor to sedentary behavior is playing video games, a wide spread and popular activity among adolescents [18-20]. In the USA, an average of almost two hours per day playing video games was reported for 8–18 year olds, with an increase of almost one hour per day from 1999 to 2009 [18]. Recent evidence indicates that in the Netherlands, about 80% of the adolescents (12–16 years old) play video games regularly and play on average five days a week with an average duration of 65 minutes on a school day and 80 minutes on a weekend day [19]. In the Netherlands time spent on playing video games seems to peak during adolescence [20,21].

Reducing time spent in sedentary video games (hereafter called non-active games) may thus contribute to reducing sedentary time and prevention of overweight and obesity in adolescents. A new generation of video games, the ones that require physical activity to play the games –i.e. active games– seems a promising alternative to traditional non-active games to promote PA and reduce sedentary behaviors in youth. These active games, such as provided by and on Nintendo Wii, Microsoft Kinect, and Sony PlayStation Move, require whole-body movement to play the video game instead of the small movements of fingers and wrists used in non- active gaming [22]. Results from various studies have suggested that energy expenditure may be substantially increased when playing active games compared to energy expenditure during non-active gaming and other sedentary screen activities such as watching television [23,24]. Active games can generally elicit light to moderate intensity physical activity (2–6 metabolic equivalents; METS) [23,24]. Consequently, when adolescents substitute the time they spent playing non-active games by playing active games, sedentary time will be reduced and physical activity increased, which may help to prevent excessive weight gain.

The potential strength of these active games is based on the intrinsic motivation of children to play video games. Intrinsic motivation is a construct based on the Self Determination Theory (SDT) and means that one enacts in an activity because one enjoys the activity and not because of external factors [25]. SDT posits that if one is intrinsically motivated, behavior change is more likely to be maintained [26]. Previous studies revealed that playing active games are perceived as fun and enjoyable [22]. Further, adolescents attending a low level of education are more likely to play active games frequently than those attending a higher level [19]. These results suggest that active games seem promising for reaching adolescents at risk, because they spend more time on non-active gaming and other sedentary behaviors [4,20] and are more likely to be overweight or obese [4].

Irrespective of energy expenditure, it can be hypothesized that active games may influence energy balance through reduced energy intake. Energy intake, especially the intake of snacks and sugar-sweetened beverages, is positively associated with time spent in sedentary screen activities such as watching TV en playing non-active games [16,27-30]. If active games can result in a decrease in sedentary time, it might simultaneously result in a lower energy intake. It is hypothesised that higher energy intake during sedentary activities is because they distract children from satiety cues [31]. It is possible that playing active games is less distractive than watching TV en playing non-active games [32]. On the other hand, it might also be that the physical activity required for playing active games influences appetite control [33] or may be thirst, resulting in a higher energy intake. However, up until now, little is known about energy intake during active gaming. So far only two studies have evaluated energy intake during playing active games [32,34]. Both studies showed no difference in energy intake while playing active games compared to energy intake while playing non-active games. However both studies were controlled laboratory studies and the effects of playing active at home on energy intake need to be further investigated. One randomized controlled trial with a 24-week follow-up showed a non-significant trend towards a decrease in self-reported energy intake from snacks in a home-based active gaming intervention group compared to a non-active game control group [35].

Substituting the time spent playing non-active games with playing active video games may thus reduce sedentary time, increase physical activity, reduce snacking and thereby prevent excessive weight gain in adolescents. So far only few and small scale studies have been conducted indicating that active games can decrease sedentary behavior and increase physical activity in youngsters on the short term (8 to 12 weeks) [36-39]. Other studies show that ongoing participation in active games is a problem [40,41]. To date only one well powered randomized controlled trial (RCT) on the effects of an active gaming intervention on body composition with a longer follow-up period has been conducted [35]. This trial showed a small effect of a six-months active game intervention on Body Mass Index (BMI) and body composition in 10–14 year old overweight/obese children. More evidence is needed from adequately powered studies, also including normal weight children, monitoring long term participation in the active games, and investigating long term effects [23,42].

Therefore, the current study aims to evaluate an active game intervention that incorporates motivational elements for adherence, includes a long intervention period and a comprehensive process evaluation. The intervention of the current study has four unique features that make this study worthwhile. First, so far no active game interventions were family-oriented. Parental involvement in interventions for children and adolescents has been recommended, therefore the current trial includes the family instead of only the individual adolescent [43]. Furthermore, games are often played at home and it has been recommended to change the obesogenic home environment to better facilitate and enable weight gain preventive behaviors [43]. Secondly, the current study includes several elements to promote active game play based on previous studies, such as encouraging social play and providing a variety of active games [22,44]. This is important because previous studies showed that maintaining participation in active game participation is difficult to achieve when providing active games without any additional efforts to encourage use [37,40,41]. Thirdly, previous studies mainly focused on the first generation of active games such as Dance Dance Revolution and PlayStation2®EyeToy [35-37,40,41], and as the gaming industry is evolving fast, there is a need for studies evaluating the newest generation of active games such as PlayStation® Move or Kinect games. Fourthly, to our knowledge the current study includes the longest follow up period (ten months) for an active game intervention.

The current manuscript describes the design of a trial evaluating the effects of a family-oriented active game intervention, incorporating several motivational elements. The overall study focuses on both the adolescents as well as his or her family members. The current manuscript focuses on the measurements and effectiveness among adolescents. The intervention consists of a) providing an upgrade package for the newest generation of active games (PlayStation®Move), b) an encouragement to replace at least 1 hour of non-active gaming by active gaming on the PlayStation Move, c) stimulating social play by providing an extra Move controller, and d) stimulating long term use by providing multiple active games.

We will test the following hypotheses:

1) The intervention will result in lower BMI-SDS (SDS = adjusted for mean standard deviation score using the 1997 Dutch growth study as reference), waist circumference-SDS, hip circumference and skinfold thickness compared to the control condition after four and ten months.

2) The intervention will lead to less self-reported time on sedentary screen activities compared to the control condition after four and ten months.

3) The intervention will lead to less self-reported sugar-sweetened beverages and snacks consumption compared to the control condition after four and ten months.

## Methods/Design

### Design

The efficacy of the active game intervention is evaluated in a randomized controlled trial among adolescents aged 12 to 16 years old and their families. Families are randomly assigned to the intervention or control group after baseline assessment by the researcher or research assistant using a pre-determined randomization list. The randomization list consists of a row with the numbers one and two in a random order and is based on a block randomization scheme, with blocks of 100, obtained from an online computer program (http://www.randomization.com). Participants are assigned to one of the research groups based on this randomization list in order of checking out after they finish the baseline measures. The intervention group is exposed to the active game intervention and the control group is asked to continue their normal game play behavior and they receive the material belonging to the intervention at the end of the study. Measures are taken at baseline (T_0_) (adolescent anthropometrics and questionnaire), after one month (T_1m_) adolescent questionnaire (including process evaluation for intervention group adolescents), four months (T_4m_) adolescent anthropometrics and questionnaire (including process evaluation for intervention group adolescents); and ten months (T_10m_) adolescent anthropometrics and questionnaire (including process evaluation for intervention group adolescents) (Table 1). Primary outcomes are adolescents’ measured BMI-SDS (SDS = adjusted for mean standard deviation score), waist circumference-SDS, hip circumference and skinfolds thickness. Secondary outcomes are adolescents’ self-reported sedentary behavior, and consumption of sugar-sweetened beverages and snacks. Additionally, physical activity behavior excluding active game play is assessed to check whether the active game intervention was at the expense of physical activity.

**Table 1 T1:** Design scheme

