### Sample size

Sample size calculation is performed to estimate how many adolescents should be included to detect a significant difference of 0.5 kg excess body weight between the intervention and control condition during the follow-up measurements (primary analysis). The 0.5 kg excessive weight gain is based on calculations in adults, because calculations for adolescents were lacking at that time. Adult individuals may gain on average 0.5 kg excess body weight per year, which results from an energy imbalance of only 70 Kcal per week per year [43]. We computed, based on energy expenditure studies, that an excess weight gain of 0.5 kg, may be prevented by substituting one hour per week of non-active gaming by playing active games [45]. To have sufficient power to detect a clinically relevant difference in excess weight gain of 0.5 kg (SD = 1.5 kg) between the intervention and control condition during follow up, with a power of 0.80, alpha .05 and an intraclass correlation coefficient (ICC) for within-subject clustering of observations of 0.7, 99 participants in each condition are needed. Taking into account an anticipated drop-out of 20%, a total of 119 adolescents per condition needs to be recruited.

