### Statistical analyses

First descriptive analyses are performed and data are checked for a normal distribution. Subsequently, control group and intervention group are described on baseline for demographics and outcome measures. Next, the effects of the intervention on all outcomes are evaluated by multilevel analyses. In the primary analyses, we analyze those participants which have at least one follow-up measurement in the groups they were randomized to. As a sensitivity analyses we will also impute follow-up measurements for persons with only a baseline measurement using multiple imputation with chained equations (intention to treat). Two models are constructed for each outcome measure: *model 1* adjusts for the baseline value of the outcome measure; and *model 2* additionally adjusts for demographics (age, sex, ethnicity and adolescent educational level) that are expected to associate with the outcome [3-5]. Second, analyses are performed according to the per protocol principle including the participants in the intervention group who played the Move games at least one hour per week. Adherence to protocol will be defined for each follow-up measurement separately, based on the question in the questionnaire assessing use of Move games (in hours per week) at T_1m_, T_4m_ and T_10m_. Again, two models are constructed for each outcome measure: *model 1* adjusts for baseline outcome measure; and *model 2* adjusts for demographics (age, sex, ethnicity and adolescent educational level) that are expected to associate with the outcome [3-5].

Additionally, a sensitivity analyses is performed by constructing all the models excluding the more extreme values on sedentary screen time (e.g. > 12 hours per day of non-active time). Further, if feasible (i.e. if the number of participants allows), explorative analyses are performed to check whether sex, age, adolescent educational level and ethnicity are effect modifiers, using a significance level of 0.10 because the study is not powered for detecting effect modification.

For the process evaluation, descriptive statistics are used describing the use of the Move games based on the Move game calendar over the ten months intervention period and the process evaluation measures. All statistical analyses are performed using IBM SPSS Statistics version 21 and statistical significance level is set at p < 0.05 for detecting main intervention effects and p < 0.10 for detecting effect modifiers.

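### Four unranked primary outcomes are judged at 0.05 with no rule for a positive trial, and the sample size is calculated for a variable that is none of them

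*Protocol article*

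**What the plan says.** - **Primary outcomes (Design).** Adolescents' "measured BMI-SDS (SDS = adjusted for mean standard deviation score), waist circumference-SDS, hip circumference and skinfolds thickness". The Abstract lists the same four. Neither place ranks them.
- **Hypothesis (end of Background).** Hypothesis 1 predicts lower values on all four "compared to the control condition after four and ten months".
- **Analysis (Statistical analyses).** The article says that "the effects of the intervention on all outcomes are evaluated by multilevel analyses". It adds: "Two models are constructed for each outcome measure". Model 1 adjusts for the baseline value and model 2 adds demographics. Neither is named as decisive.
- **Threshold (Statistical analyses).** The "statistical significance level is set at p < 0.05 for detecting main intervention effects". There is no lead outcome, success rule or adjustment.
- **Powered variable (Sample size).** The calculation is to detect "a significant difference of 0.5 kg excess body weight between the intervention and control condition" during follow-up, and it is labelled the primary analysis. The inputs are a difference of 0.5 kg, SD 1.5 kg, power 0.80, alpha 0.05 and a within-subject ICC of 0.7, giving 99 per arm.
- **Power claims.** The Abstract and the Discussion describe the trial as having adequate or good power, without restricting this to one outcome.

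**The concern.** Two things are unsettled, and both bear on the headline result.

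First, the article does not say what counts as success. If one significant primary outcome out of four is enough, the chance of a false claim exceeds 5%. If all four are needed, there is no inflation, but the chance of success falls below that of any single outcome. The same results could support a positive or a negative conclusion depending on the reading. The Blinding section adds weight to this: follow-up measurements are not blind, and neither are the data analyses. Whoever chooses the outcome or model to emphasise can therefore know the group labels.

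Second, the section that justifies the sample size and the section that lists the primary outcomes disagree on what the primary analysis is about. Kilograms of excess weight appears in neither list of primary outcomes. No target difference or SD is given for BMI-SDS, waist-SDS, hip circumference or skinfolds, and nothing converts kilograms into any of them.

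**Working it through.** **1. The plan's own figure.** Inputs from Sample size: difference 0.5 kg, SD 1.5 kg, two-sided alpha 0.05 (assumed two-sided, as sidedness is not stated), power 0.80.

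n per arm = 2 × [SD × (1.960 + 0.842) / difference]² = 2 × (1.5 × 2.802 / 0.5)² = 141.3

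Multiplying by the ICC gives 141.3 × 0.7 = 98.9, so 99. The usual factor for the mean of two follow-up measurements is (1 + 0.7)/2 = 0.85, which gives 120.1, so 121. The stated 99 is thus recovered only with the factor 0.70. That is a separate matter. What counts here is that every input is in kilograms of weight and that alpha is spent once, on one variable.

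**2. Familywise error if any one primary outcome suffices.** There are four tests at 0.05, one contrast and one model per outcome.

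- Independent tests (upper figure): 1 − 0.95⁴ = 18.5%.
- Correlated tests: multivariate normal simulation with equal correlation r between outcomes. The article gives no correlations, so r is an assumption, shown as a range.

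| Assumed r | Any of four, two-sided | Any of four, favourable direction only |
|---|---|---|
| 0.5 | about 15.6% | about 7.8% |
| 0.8 | about 11.4% | about 5.8% |

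The reference is 5% for the two-sided column and 2.5% for the favourable column. In both, the inflation is about two- to three-fold.

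**3. If each visit were tested separately.** There would be eight tests. With r from 0.8 to 0.5 and correlation between visits from 0.8 to 0.6 (assumed), the two-sided figure is about 17–26%. The article does not say that this is what will be done.

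**4. If all four must succeed.** Type I error is not inflated. If each outcome had 80% power, joint power would be about 56% (r = 0.5) to 66% (r = 0.8). This is illustrative only, because no power has been established for any of the four.

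**5. What 99 per arm can detect on any one outcome.** Detectable standardised difference = 2.802 × √(2 × factor / 99):

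- factor 0.70 (the one that recovers 99): 2.802 × √(1.40/99) = 0.333
- factor 0.85 (two follow-ups, ICC 0.7): 2.802 × √(1.70/99) = 0.367
- factor 1 (no gain from repeated measures): 2.802 × √(2/99) = 0.398

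The first equals 0.5/1.5, as it should. To express these in BMI-SDS, multiply by an SD that the article does not give.

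**6. Cost of keeping four primary outcomes.** At the Bonferroni level of 0.05/4 = 0.0125 and a standardised effect of 0.333 (assumed to apply), power at 99 per arm is 0.62 with factor 0.70 and 0.52 with factor 0.85. For 80% power, 141 or 171 per arm would be needed. Holm is never less powerful than Bonferroni for any single outcome, so these power figures are floors for it.

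**The case against.** The strongest reply is that this is a condensed article. The multiplicity procedure, the decisive model and the decisive contrast often sit in an analysis plan, which is not shown. Silence on those details alone would not be a finding. What remains is what the article itself fixes: four unranked primary outcomes, a single threshold for main effects, and a sample size for a variable outside the list. A later analysis plan could supply a decision rule, but it could not make a calculation in kilograms apply to hip circumference or skinfolds.

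Two further objections limit the size of the point:

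- The two-sided error rates include significant results in the harmful direction, whereas hypothesis 1 predicts lower values. The chance of a false claim of benefit is about half as large, 6–8%. This stands, though the nominal rate halves too.
- Weight is measured at each anthropometric visit and enters BMI-SDS, so the powered quantity is related to one primary outcome. That also stands, but no conversion is given, and it does not help the other three.

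A reader might infer more than the text supports:

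- **That four and ten months are each tested at 0.05.** Hypothesis 1 names both visits, but Statistical analyses specifies no test per visit. The within-subject ICC in Sample size fits a single effect pooled over follow-up equally well. The 17–26% figure is therefore conditional.
- **That the two models are two further independent chances of success.** They estimate the same comparison with different covariates and will be strongly correlated.
- **That the skinfold outcome is contradictory.** The Abstract specifies "waist circumference-SDS, hip circumference and sum of skinfolds". The shorter label in Design is loose wording compatible with a sum.

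**Conclusion.** The point holds for two defects that the article itself contains. First, four unranked primary outcomes are judged at 0.05 with no statement of what makes the trial positive. If any one counts, the two-sided familywise error is about 11–16% (18.5% if independent), or about 6–8% against 2.5% in the favourable direction. These figures rest on assumed correlations between outcomes of 0.8 to 0.5, and on one contrast and one model per outcome. If all four must succeed, the error is not inflated and the problem is power instead.

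Second, the stated 80% power belongs to 0.5 kg excess body weight and to none of the four primary outcomes. This needs no assumption, since it follows from comparing Sample size with Design. It does not show that the trial is underpowered for BMI-SDS or the others, because the article gives no figures from which to judge that. It shows that the general claims of adequate power have no calculation behind them for any declared primary outcome.

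**What to change.** Before outcome data are analysed:

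1. Name one lead primary outcome. BMI-SDS is the natural choice, as it is listed first and is closest to the weight variable that was powered.
2. Attach to it one contrast (the effect pooled over follow-up, or the ten-month effect) and one model. Nothing in the article favours a particular contrast or model. Fixing one in advance is what matters.
3. Make waist-SDS, hip circumference and skinfolds secondary. Alternatively, keep all four as primary with Holm adjustment and say that any one suffices.
4. Reconcile Sample size with Design. State the standardised difference detectable for the lead outcome (0.333 on the article's implied factor, up to 0.398 with no repeated-measures gain). Convert it to BMI-SDS units with an explicitly assumed SD.
5. Restrict the power claims in the Abstract and Discussion to that outcome.

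The cost is changed wording, a registry update and a short recalculation that needs an SD from outside the article. The real downside is that three outcomes lose primary status. If all four are kept, each faces a stricter level, and power for a single outcome could be as low as 0.52–0.62 at 99 per arm under the assumptions in the working.
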